**Supplemental Protocol**

**Title:** **Safety of Maraviroc for post-stroke depression**

**Introduction:**

# Posts-stroke depression (PSD) is the most frequent neuropsychiatric sequela of stroke, with a prevalence rate of 18 to 61% (a 3-fold increase when compared with the general population)^1,2^. PSD is associated with increased mortality, higher disability, lower quality of life and a greater risk for cognitive decline^3,4,5^. Despite significant clinical relevance, the relationship between stroke and depression, assumed to be multifactorial, remains poorly understood, and specific mechanism-based treatment targets are lacking.

Currently there are no "gold standard" therapies for PSD or post stroke anxiety symptoms. Therapeutic options do not differ from those recommended to the general population, but controlled clinical trials examining their efficacy in this specific sub group of patients demonstrated conflicting results, and two recent randomized control trials using fluoxetine and escitalopram (both specific serotonin reuptake inhibitors – SSRI's) in this population showed no significant efficacy^6,7^.

# Although multiple treatments for Major depressive disorder (MDD) are available, nearly 30 to 50% of patients do not fully remit from the disorder using current biogenic amine-based antidepressant drugs^8,9^. Limitations of currently available antidepressants include delayed onset of therapeutic action, troubling side effects and low remission rates after multiple courses of pharmacotherapy. Indeed, the large-scale Sequenced Treatment Alternatives to Relieve Depression trial (STAR*D) demonstrated that for 70% of patients, a single treatment trial with a SSRI did not bring upon remission^10^. After 2 sequential treatment interventions remission rates were only 50% to 55%, and the probability of achieving remission with third- and fourth-step therapy options was considerably lower^11^.

Elderly patients and stroke survivors are especially susceptible to side effects that can limit the use of SSRI's, such as hyponatremia. In addition, meta-analyses demonstrate that SSRI's have little to no effect on cognitive function^12^, an important component of post-stroke recovery, with much influence on emotional sequelae.

# Accumulating evidence suggests that inflammatory processes and neural-immune interactions are involved in PSD. Related theories focus on synaptic plasticity as an important means of recovery from PSD, after converged molecular and cellular mechanisms including inflammation cause atrophy of neurons, loss of glutamatergic synaptic connections and dysfunction of the circuitry that is essential for mood regulation and cognitive function^13,14^. Indeed, PSD can be perceived as a psychoneuroimmunological disorder in which inflammatory mechanisms involving cytokines and chemokines play a crucial role^15,16^. Both acute stroke patients and depressed patients consistently show higher levels of pro-inflammatory cytokines, acute phase proteins, chemokines and cellular adhesion molecules^17,18.^.This suggests that psychotropic drugs that have central anti-inflammatory properties may serve as a mechanism based treatment option for depression, thus providing a new mode of treatment..

**The C-C chemokine receptor type 5 (CCR5),** is known to be involved in immune processes and neuroplasticity, and is highly expressed in T cells and macrophages, as well as microglia, astrocytes and neurons in multiple brain regions. CCR5 is a pro-inflammatory receptor and inhibition of its signaling has been shown to enhance plasticity processes in hippocampal and cortical circuits^19^. Other reports show that CCR5 blockade attenuated activation of glial cells, maintained the integrity of endothelial monolayer, reduced the infiltration of T cells, and attenuated neuroinflammation^20^.

We have recently tested the effects of the naturally occurring CCR5-Δ32 mutation in 435 post-stroke patients (the TABASCO prospective cohort). In this cohort, about 15% of patients, mostly Ashkenazi Jewish individuals, were carriers of the mutation. This group showed significantly better cognitive and functional outcome 2 years post-stroke^20^. Unpublished data further demonstrated that this sub group of patients had also significantly less depressive and post-traumatic symptoms, 6 and 12 and 24 months after the index event, implying that impaired activity of the CCR5 may have therapeutic advantages in both stroke cognitive recovery and depressive symptoms alleviation. Our findings suggest that the anti-depressive effect of the mutation might even be greater than its "cognitive protection" effect. Interestingly, Ogłodek et al. in her studies found a remarkable rise in the level of CCR5 and its chemokines in serum from patients with depression and post-traumatic stress disorder (PTSD)^21-23^.

On this basis, we suggest repurposing **Maraviroc** (Selzentry), the Food and Drug Administration (FDA) approved CCR5 antagonist for R5-tropic HIV-1 infected patients, as a new mechanism-based treatment option for PSD.

Together with our colleagues, we have recently shown^20^ that Maraviroc modulates several parallel signaling cascades implicated in learning, memory and in depression, including the suppression of adenyl cyclase ^,24,25^, as well as the activation of the PI3K/AKT and P44/42 MAPK signaling^26^. These findings support the application of brain permeable CCR5 antagonists, not only as a combination drug in antiretroviral therapy, but also as a treatment for cognitive deficits and depression caused by HIV. We offer using this same drug, that mimics the action of the CCR-5 mutation as novel treatment option for PSD.

# Toxicology

Maraviroc is the only CCR5 antagonist currently approved by the FDA, the European Commission and the Health Canada for treatment of patients infected with R5-tropic HIV-1. The drug is a small molecule metabolized by CYP3A4, with a good pharmacokinetic profile, relatively low protein binding and high bioavailability when given at standard doses twice a day. Maraviroc appears to be well tolerated, but the dose has to be adjusted when given with CYP3A4 inducers or inhibitors, primarily drugs that are also used for HIV therapy, but also for several anticonvulsants. Patients who take these medications will be excluded from the proposed trial. The drug should be used cautiously in patients with a history of orthostatic hypotension and patients with pre-existing liver dysfunction or co-infection with hepatitis B or C (these patients will also be excluded from the proposed trial). Maraviroc does not appear to cause clinically significant changes in concentrations of other medications. It is moderately lipophilic, so it can penetrate the blood-brain barrier. At a single dose of 150 mg or 300 mg, time to maximum concentration occurred by 2 hours post-treatment in humans. The terminal half-life is 14-18 hours, so a single dose used in the proposed protocol should be adequate, rather than the twice-daily (BID) treatment for AIDS.

**Based on Pfizer’s reports on premarketing and post marketing studies of Maraviroc and review of the literature, no dose adjustment is necessary even in patients with mild-to-moderate renal impairment. The drug does not affect the QT interval.** **At high doses (600 mg or more), it may induce orthostatic hypotension, so it is recommended that users who also take antihypertensive medications be asked about symptoms of orthostatic hypotension.** Of note, 8% of patients in active and placebo drug groups described orthostatic symptoms in a large trial. In HIV trials, 1.3% of subjects had cardiovascular events, more than in the placebo group, but the link to the drug was unclear and symptoms occurred only in those with known cardiac disease. Also, no greater incidence of infection, rash or other CNS symptoms were noted in these patients. **An occasional Stevens-Johnson syndrome and drug rash with eosinophilia and systemic symptoms did occur (seen only in postmarketing surveillance, not in controlled trials), so complaints of rash, fever, joint or muscle aches, blisters, facial edema etc. will be part of our weekly phone call surveillance plan. Participants will be told to stop their medication immediately should such symptoms occur, and their physician will be notified.** Of note, St John’s wort should not be used with Maraviroc, since it decreases the concentration of the medication.

**Maraviroc is metabolized by the liver, so using it in persons with more than mild hepatic disease, especially in the presence of a CYP3A inhibitor, would have to be closely monitored; we will therefore not include these patients in this study.**

Clinical aspects

**Pharmacokinetics**: Maraviroc pharmacokinetics was studied in 28 phase I/IIa studies (complete profiles) and 3 phase IIb/III studies (with sparse sampling). The evaluation was performed after single-dose intravenous administration (1–30 mg) as well as oral single-dose (1–1200 mg) and multiple-dose administration (3–900 mg twice daily [BID] and 1200 mg once daily [QD]). The following formulations were used during development: powder for oral solution in phase I, 5 mg/25 mg/50 mg/100 mg/150 mg tablets in phase I/IIa and 150 mg in phase IIb/III. An intravenous formulation was used to determine absolute bioavailability. The commercial formulations (150 mg, 300 mg) were not used in the clinical trials. The analytical methods used to analyze Maraviroc have been adequately validated.

**Absorption**: The absorption of Maraviroc is highly variable with multiple peaks. The mean Tmax was between 2 and 3 hours with individual values ranging from 0.5 to 8 hours (with food). The absolute bioavailability for Maraviroc was 23% at 100 mg, and it has a predicted bioavailability of 31% at 300 mg. The absorption of Maraviroc is dose dependent, likely attributed to saturated efflux transporters in the intestine. Maraviroc is highly soluble in aqueous media across pH 1–7.5, has an efflux ratio >10 in Caco-2 cell monolayers and is a substrate for P-gp and the multidrug resistance protein.

**Bioequivalence:** The commercial tablet formulations (150 mg, 300 mg) are completely dissolved within 30 minutes (>90% within 15 minutes), and hence, dissolution will not be rate limiting for the absorption of Maraviroc. Bioequivalence was shown between the commercial 300 mg tablet and research formulation (2 x 150 mg). The solution had a 12% higher bioavailability than the research tablet.

**Metabolism**: The metabolism of Maraviroc was evaluated in 3 healthy male subjects after administration of 300 mg 14C Maraviroc as an oral solution in a fasted state. Whole blood samples and plasma samples were collected on days 1 to 6 at specified times up to 120 hours post-dose to measure plasma Maraviroc and metabolite UK-463,977 concentrations and radioactivity and for metabolite profiling, respectively. Urine and feces were collected to measure urinary and fecal radioactivity and for metabolite profiling up to at least 120 hours post-dose on day 1. UK-463,977 concentrations were also determined in urine. Unchanged Maraviroc was the main circulating component in plasma (42% of plasma radioactivity), and the metabolites UK-408,027 (22%), an amine analogue (11%) and UK-463,977 were also identified in plasma. The metabolites UK-408,027 or UK463,977 appear not to accumulate with time.

Maraviroc achieves concentrations within the EC90 range in CSF and showed viral suppression in CSF. The CSF:plasma ratio of Maraviroc was reported as 0.03 (0.01–0.10) ^27,28^.

**Hepatic impairment**: A study involving patients with mild and moderate hepatic impairment (Child-Pugh A and B) as well as individuals with normal hepatic function has been conducted^29^. Administration of Maraviroc (300 mg single dose) to patients with mild and moderate hepatic impairment resulted in mean values of area under the curve (AUC) last that were 25% and 45% higher, respectively, than in individuals with normal hepatic function (geometric means and corresponding 90% confidence intervals [CI] for the comparisons were 125% [84.7%, 185%] and 145% [100%, 212%]). Smaller differences in Cmax were noted with mean values 11% and 32% higher for mild and moderate impairment compared to normal function, respectively. As expected, mean CL/F decreased with increasing hepatic impairment, although the differences between mild hepatic impairment and normal hepatic function were minimal. Mean renal clearance (CLR) was higher in individuals with moderate hepatic impairment compared to those with normal hepatic function. The mechanism for this increase in CLR is not known. Mean Tmax and t1/2 did not appear to be affected by hepatic impairment. The data are limited with wide confidence intervals for the comparisons to individuals with normal hepatic function.

**Renal impairment**: Studies in patients with renal impairment have not been performed. In patients without concomitant administration of CYP3A4 inhibitors, renal excretion constitutes a minor elimination pathway (about 23% of total clearance). In these patients, decreased renal function will likely have a limited effect on Maraviroc exposure. In patients with concomitant administration of CYP3A4 inhibitors, e.g., protease inhibitors, renal clearance will constitute up to ~ 70% of total clearance.

Clinical safety

Phase 1 single- and multiple-dose studies in healthy volunteers, conducted in 2001 and the first half of 2002, demonstrated that Maraviroc was safe and well-tolerated in multiple doses up to 300 mg BID, that it had a pharmacokinetic profile compatible with QD or BID oral dosing, that it could be combined with other antiretrovirals and that doses ≥100 mg BID resulted in exposure above the geometric mean antiviral IC90 in vitro.^30,31^

**Patient exposure in phase II studies:** 595 healthy patients and 37 patients with HIV have been exposed to Maraviroc in doses ranging from 1–1200 mg. In 2 multiple dose-finding phase II studies, 66 patients with HIV were exposed to Maraviroc (25–300 mg) for 10 days. Long-term safety data (minimum 24 weeks) were obtained in the main and supportive studies. In addition to the 3 previously presented studies in treatment-experienced patients (A4001027, A4001028 and A4001029), supportive safety data (*n* = 174) were provided from an ongoing study in treatment-naïve patients (A4001026). In this study, a Maraviroc treatment arm (300 mg QD) was stopped due to an increased incidence of treatment failure, and Maraviroc 300 mg BID open-label was offered. A total of 964 treatment-experienced patients received at least 1 dose of Maraviroc, including 840 CCR5-positive patients in the 2 pivotal studies. In the 2 pivotal trials (A4001027, A4001028), patients were exposed to Maraviroc for a median of 8 months); the total exposure (580 patient years) was around five-fold that of placebo exposure (124 patient years).

**Adverse events (AEs):** AEs were similar in frequency and character in patients treated with Maraviroc or placebo and were expected in this treatment population. Furthermore, no relevant differences in AEs (including serious AE) were seen in Maraviroc given QD versus BID. Infections (upper respiratory and herpes simplex) were somewhat more common with Maraviroc than with placebo, also after adjustment of exposure. Herpes simplex as a manifestation of immune response inflammatory syndrome (IRIS) is a well-known phenomenon and could be one possible explanation for this particular finding. AIDS-related infections and malignancies were not more common with Maraviroc, and autoimmune disorders were not reported. No major safety concerns were found with Maraviroc as part of the antiretroviral regimen in treatment-experienced patients. The dose-limiting adverse event, postural hypotension, appeared to be clinically manageable with the chosen dosage of 300 mg. Maraviroc was well tolerated, with the same frequency of study-drug discontinuation for Maraviroc and placebo. The spectrum of AEs reported, including serious AEs and deaths, did not reveal any specific issues considering the population studied. The frequency of liver-related AEs does not raise any concerns for liver toxicity. In late 2004, four large studies were initiated (phase IIb and phase 3), with 4794 patients screened at more than 200 sites in the United States, Canada, Europe, Australia, South Africa, Mexico and Argentina. An in-depth review of all data for evidence of hepatotoxicity for MVC and a high level of vigilance for any signals did not find any evidence for a systematic increase in hepatic enzymes or other markers for hepatotoxicity. Shortly afterward, concerns were raised regarding a potential increased risk for certain malignancies, and initially, there were concerns that this could be a class effect based on the immune-modulatory potential of CCR5 antagonists, but review of data from other vicriviroc studies, as well as the MVC studies, did not support this theory.^32^

Maraviroc (150 mg and 300 mg BID) received approval for use in the United States in August 2007 and in the European Union in September 2007.

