# This study will evaluate the safety and efficacy of Maraviroc 300 mg per day in patients suffering from PSD.

Primary objective:

1. To investigate the safety and tolerability of Maraviroc 300 mg per day in subjects with PSD.

Secondary Objectives:

1. To investigate the safety and tolerability of Maraviroc 300 mg in PSD subjects, with special attention to: effects on heart rate and blood pressure.
2. To evaluate the efficacy of Maraviroc 300 mg per day in improving depressive symptoms in subjects with PSD, as assessed by a change from baseline in the Montgomery-Asberg Depression Rating Scale (MADRS) total score and in improving cognitive, functional, and behavioral outcomes.

To evaluate the effect of treatment with Maraviroc 300 mg per day for 10 weeks on blood inflammatory markers in subjects with PSD.

3. To assess the effect of Maraviroc 300 mg in PSD subjects on: a. Depressive symptoms, as assessed by the 16-item Quick Inventory of Depressive Symptomatology- Self Report (QIDS-SR16) b. Remission, defined as a MADRS total score ≤10 c. Response, defined as a ≥50% reduction from baseline in MADRS total score d. The severity of illness using the Clinical Global Impression - Severity (CGI-S) and the Patient Global Impression - Severity (PGI-S) e. Symptoms of anxiety as assessed by the Generalized Anxiety Disorder 7-item Scale (GAD-7). d. Cognitive status, as assessed by cognitive score based on repeatable computerized battery of cognitive tests (Neurotrax) and Montreal Cognitive Assessment (MoCA). e. Functional outcome, as assessed by the stroke impact scale (SIS), the activities of daily living (ADL) score, and Reintegration to Normal Living Index (RNL).

Methods

We plan to enroll ten adults with PSD.

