**Exclusion Criteria:**

1. Hemorrhages and cerebral edema (e.g., subarachnoid haemorrhage, intracerebral hemorrhage, subdural hematoma, epidural hematoma)
2. Patients in a state of coma or with severe disturbance of consciousness, aphasia, agnosia, or deafness that subsequently affects expression and communication.
3. Significant acute medical illness including: drug overdose, severely disturbed liver, kidney or lung function, anemia, hypothyroidism, or uncontrolled diabetes.
4. Significant acute neurologic illness including: impaired consciousness, Parkinson's disease, Huntington's chorea, progressive supranuclear paralysis, brain tumor, subdural hematoma, multiple sclerosis, hydrocephalus, Binswanger's disease, or severe aphasia
5. Patients diagnosed with dementia or major neurocognitive disorder as defined by DSM-5at screening, or other neurological conditions that might dominate the clinical picture (multiple sclerosis, Parkinson's disease, epilepsy, Huntington's chorea, progressive supranuclear paralysis, brain tumor, subdural hematoma, multiple sclerosis, hydrocephalus, Binswanger's disease, etc.)
6. Subject has a history of human immunodeficiency virus (HIV), hepatitis B surface antigen (HBsAg) or hepatitis C antibody (anti-HCV) positive, or other clinically active liver disease, or elevated hepatic transaminases or bilirubin, or tests positive for HIV at Screening.
7. History of renal insufficiency or serum creatinine over 1.6;
8. Subject has a current or past diagnosis of bipolar or related disorders, intellectual disability, cluster B personality disorder (e.g., borderline personality disorder, antisocial personality disorder, histrionic personality disorder, and narcissistic personality disorder), psychotic disorder, schizophrenia, PTSD , and substance/alcohol use disorders other than nicotine in the past year (including barbiturates, methadone, opiates, cocaine, cannabinoids, and amphetamine/ methamphetamine).
9. Subject has suicidal ideation with intent to act during the screening phase or on Day 1 per investigator’s clinical judgment, or has a history of suicidal behavior within the past year; or subject has homicidal ideation/intent at Screening or on Day 1.
10. Subject has a history of malignancy within 5 years before screening (exceptions are squamous and basal cell carcinomas of the skin and carcinoma in situ of the cervix, or malignancy that in the opinion of the investigator is considered cured with minimal risk of recurrence).

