11. Subject has known allergies, hypersensitivity, intolerance, or contraindication to Maraviroc or its excipients.
12. Subject has received an investigational drug (including investigational vaccines) or used an invasive investigational medical device within 60 days before the planned first dose of study drug or is currently enrolled in an investigational study.
13. Subject is a woman who is pregnant, breast-feeding, or planning to become pregnant while enrolled in this study or within 3 months after the last dose of study drug.
14. Subject has any condition for which, in the opinion of the investigator, participation would not be in the best interest of the subject (e.g., compromise the well-being) or that could prevent, limit, or confound the protocol-specified assessments.
15. Subject has had major surgery, (e.g., requiring general anesthesia) within 2 weeks before screening, or will not have fully recovered from surgery, or has surgery planned during the time the subject is expected to participate in the study.
16. Use of drugs with possible interactions with Maraviroc.

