**Recruitment and retention plans**

Screening and patient evaluation:

Participants will be out-patients referred from the community or the hospital’s ambulatory services, who meet entrance and exclusion criteria. After receiving a detailed explanation and signing informed consent, the participant will be further screened. All identifying information of participants will be saved in a separate password protected study log available only to study investigators. All the gathered data will be de-identified and coded with a pre-assigned study ID.

Eligible patients enrolled in the study will undergo a baseline visit (Week 1), in which they will receive the study drug following completion of all relevant assessments. During the first administration, participants will remain under clinical supervision and vital signs monitoring for 2 h at the Tel Aviv Sourasky Medical Center. Blood pressure and heart rate will be recorded before discharge. Patients will be evaluated every 2 weeks during the trial using multiple depressive, anxiety and functional questionnaires as well as cognitive tests. A final safety and efficacy assessment will be held 8 weeks after the patient’s last dose (Week 18).

Open-label treatment period:

On Day 1, subjects will start the study drug. A 1-week supply of capsules will be handed to participants after the consent has been signed, and baseline measurements obtained, usually on the same day. The second 2-weeks supply will be provided during a scheduled interim measurement assessment at TLVMC near the end of the 2nd week on medication. Participants will take Maraviroc 300 mg at 6-8AM. The capsules will be supplied by the hospital pharmacies and used under IRB approval as required.

The efficacy, safety, and biomarker evaluations that will be performed at each visit of the treatment phase and are described in the Time and Event Schedule.

Post-treatment phase

The efficacy and safety evaluations that will be performed at each visit during the post-treatment phase are described in the Time and Event Schedule.

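### The Toxicology section can fairly be read as excluding patients with a history of orthostatic hypotension, but no numbered criterion does so

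*Protocol*

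**What the plan says.** The Toxicology section of the protocol first excludes patients taking drugs that induce or inhibit CYP3A4. The next sentence advises caution in certain groups and closes with an exclusion: "history of orthostatic hypotension and patients with pre-existing liver dysfunction or co-infection with hepatitis B or C (these patients will also be excluded".

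The Exclusion Criteria take up the liver and hepatitis part. Item 6 names "hepatitis B surface antigen (HBsAg) or hepatitis C antibody (anti-HCV) positive, or other clinically active liver disease", and item 3 covers severely disturbed liver function. Interacting drugs are covered by item 16 and by the Prohibitions and Restrictions. Orthostatic hypotension has no item of its own. The nearest is the catch-all item 14: "Subject has any condition for which, in the opinion of the investigator, participation would not be in the best interest of the subject".

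Orthostatic or postural hypotension comes up in two other places:

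- Later in Toxicology: "At high doses (600 mg or more), it may induce orthostatic hypotension", with the advice that "it is recommended that users who also take antihypertensive medications be asked about symptoms of orthostatic hypotension".
- In the adverse events paragraph under Clinical safety: "The dose-limiting adverse event, postural hypotension, appeared to be clinically manageable with the chosen dosage of 300 mg".

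The first secondary objective gives special attention to "effects on heart rate and blood pressure".

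**The concern.** Eligibility is applied from the numbered lists. If the Toxicology sentence states an exclusion that the lists omit, a screener following the lists could enrol a patient whom the protocol elsewhere says it will not take.

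The omission bears on safety. The condition is a history of the same kind of event that the protocol calls dose-limiting for this drug, and blood pressure is a named safety objective. The Safety Plan also says that the eligibility criteria were built to keep out patients at higher risk of toxicity. A group that the protocol itself singles out for caution is an obvious candidate for such a criterion.

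**Working it through.** No arithmetic applies beyond a count, so the check sets the statements side by side.

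**Step 1: what the Toxicology sentence covers.** It has two groups, each introduced by its own mention of patients: (a) prior orthostatic hypotension, and (b) liver dysfunction or hepatitis B or C co-infection. One expression of caution governs both. The parenthesis excluding these patients comes at the end. It can refer to (a) and (b) together, or to (b) alone.

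**Step 2: where each excluded or cautioned group reaches the operative text.**

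| Group in Toxicology | Operative criterion |
|---|---|
| Users of interacting drugs | Exclusion 16; both prohibitions |
| Liver dysfunction | Exclusions 3 and 6 |
| Hepatitis B or C | Exclusion 6 |
| History of orthostatic hypotension | None |

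Criteria naming orthostatic or postural hypotension: 0 of 6 inclusions, 0 of 16 exclusions, 0 of 2 prohibitions; 0 of 6 + 16 + 2 = 24 in all.

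**Step 3: could a general criterion do the work?**

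- Exclusion 11 covers a contraindication to Maraviroc. Toxicology describes orthostatic hypotension as a reason for caution, which is not the same thing.
- Exclusion 14 depends on the investigator's opinion of the individual patient. It permits exclusion but does not apply a categorical one.

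**Step 4: does other text decide between the readings?**

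- For the narrow reading: later in Toxicology, patients with more than mild hepatic disease are again said not to be included, while orthostatic hypotension is met with symptom questions to users of antihypertensives. The Interventions section that deals with liver tests describes participants as having neither hepatic nor renal impairment and does not mention blood pressure.
- For the broad reading: one expression of caution covers both groups, and the Safety Plan states the general aim of excluding patients at higher risk.
- Neither side is decisive. Questioning antihypertensive users about symptoms is monitoring, and it is compatible with excluding or admitting patients who have a history. The Safety Plan's aim does not name the condition.

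**Result.** On the broad reading, a stated exclusion is missing from the list. On the narrow reading, the list is complete and the parenthesis is loosely worded. Either way one edit is needed.

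**The case against.** The strongest reply is that nothing is missing. The noun is repeated, so the parenthesis attaches naturally to the second group. Every later statement about who will not be enrolled concerns organ impairment, and none concerns orthostatic hypotension. Recruitment and retention plans says that participants are those who meet the entrance and exclusion criteria. A screener therefore has one rule to follow: such a history is not an automatic exclusion, and item 14 is available, informed by the medical history and vital signs collected at screening. In a single-center trial of 10 patients, inconsistent application is unlikely to be a large problem.

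The safety stakes are also limited by the protocol's own account. Induced orthostatic hypotension is tied to 600 mg or more, against 300 mg once daily here. Orthostatic symptoms are reported in 8% of patients in both active and placebo groups of a large trial. The event is called manageable at the chosen dose. The first dose is supervised: "During the first administration, participants will remain under clinical supervision and vital signs monitoring for 2 h".

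Much of this stands. The narrow reading is plausible, and the broad one cannot be called the only or the clearly preferred one. The risk arguments lower the weight of the point. They do not say which patients the Toxicology parenthesis covers, and supervision of the first dose begins only after the patient has been enrolled.

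Two stronger inferences should be resisted:

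- A reader might conclude that the primary safety endpoint is in jeopardy, because it tolerates no serious treatment-emergent event and no discontinuation for one. The documents give neither the frequency of such a history in this population nor an event rate in these patients at 300 mg, so no such effect can be shown.
- A reader might treat the lack of a specified standing blood pressure reading as part of the same defect. It is a separate matter of how vital signs are taken, and it contradicts nothing in the text.

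**Conclusion.** The point holds as a modest eligibility inconsistency with a safety bearing. The Toxicology section can fairly be read as excluding patients with prior orthostatic hypotension, none of the 24 operative criteria does so, and the list as written admits them unless the investigator uses exclusion 14.

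The conclusion rests on the broad reading being reasonable, not on its being the only one. It claims no excess risk at 300 mg once daily. Sample size, endpoints and analysis are unaffected. The change is worth making because it is cheap and concerns the adverse event that the protocol calls dose-limiting.

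**What to change.** Add an exclusion 17, *History of orthostatic hypotension*, checked from the medical history already taken at screening. This needs no new procedure. The cost is that a few candidates may be lost in a trial of 10, and that the tolerability findings would not extend to patients with such a history.

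If the sponsor meant only the second group, reword the Toxicology parenthesis so that it names patients with liver dysfunction or hepatitis B or C as those excluded. That costs one phrase. Patients with prior orthostatic hypotension would then be knowingly admitted. In that case, taking a standing reading within the vital signs already scheduled at screening, Day 1 and weeks 2, 4, 7 and 10 would be a sensible optional precaution; resolving the inconsistency does not require it.
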